#### Discontinuation criteria

A physician responsible for diagnosis assesses exacerbations of PHN occurring during the study, and when a patient experiences facial pain symptoms that persisted despite acupuncture treatment, as indicated by a VAS score exceeding 8, the physician evaluates the severity and subsequently discontinues the study;The specialist assesses the occurrence of significant adverse reactions during the study to make a decision on whether to proceed or discontinue the research;Participants who encounter severe complications or illnesses during the study that necessitate urgent medical attention; andParticipants who have additional reasons that prevent them from continuing with this study.

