#### Elimination criteria

Self-withdrawal or loss of visits by subjects;Those who have not reached 2 treatments; andThose who experience serious adverse reactions or adverse events during treatment.

(Note: Subjects who are dislodged should be accounted for, and their study medical records should be retained for review and not included in the final statistical analyses.)

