### Randomization and allocation concealment

The envelope randomization method will be used for randomization. Upon meeting both the inclusion and exclusion criteria, subjects will be enrolled into the study. The randomization personnel or clinical researchers will randomize them based on the pre prepared patient grouping envelopes. The randomization protocol for this study will be generated by the Clinical Evaluation Center at the subject’s institution, and this person will be not involved in the statistical analysis of this project. The randomization scheme for this study and the individual parameters set in the process of generating that scheme are collectively referred to as the blind bottom, which is sealed and signed by the person generating the randomization scheme and kept by a dedicated subject matter manager not involved in this project. Participants in subgroups are not involved in the statistical analysis of data. The evaluation of the efficacy indicators will be collected and organized by a person who is unaware of the subgroups, with a triple separation of the researcher, the acupuncture operator, and the statistician.

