### Blinding

Because this project is a needling treatment, the needling operator must be in direct contact with the patient, to whom blindness cannot be applied. However, blinding is implemented for all other personnel involved in the study (including patients, those who recorded and entered the observational indicators, and the data statisticians), who will be unaware of the specific grouping of patients. To guarantee a more effective execution of the blind approach, each patient will be treated individually as much as possible, minimizing the need for patients to discuss with each other about the acupuncture treatment method, their feelings during the acupuncture, and the effects of the treatment.

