#### Medication group

In this group, participants undergo treatment through the oral ingestion of pregabalin capsules (specification: 75 mg*8 capsules, manufactured by Pfizer Pharmaceutical Co., Ltd.) only, 150 mg each time, twice a day, for 4 consecutive weeks.

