#### Safety evaluation related to EA

Broken needles, missed needles, needle fainting, unbearable acupuncture-induced pain (VAS ≥ 8 points), localized hematomas, infections, and abscesses; symptoms, mean degree, and mean duration of other post-acupuncture discomfort (encompassing pain, dizziness spells, anorexia, headache, and insomnia that occurred ≥1 h in duration after acupuncture).

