## Conclusion

In summary, this research protocol is a multicenter, randomized controlled trial with blinding of both patients and assessors. The objectives are to evaluate the effectiveness and safety of EA compared with medication; and to clarify whether EA in the treatment of cephalo-facial PHN has a clear and stable advantage over oral pregabalin alone in terms of improvement in mood, quality of sleep, and quality of life. This finding will provide new scientific and effective ideas for the clinical treatment of PHN.

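### The only pain-severity stopping rule (VAS above 8) is worded for acupuncture-treated patients, so read literally it cannot apply to the pregabalin arm and conflicts with the stated blinding

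*Protocol article*

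**What the plan says.** The Discontinuation criteria of the protocol article have four items. The first gives a diagnosing physician the task of assessing PHN exacerbations. It sets the only numerical pain threshold: it applies "when a patient experiences facial pain symptoms that persisted despite acupuncture treatment, as indicated by a VAS score exceeding 8", after which the physician evaluates severity and discontinues. The other three items cover significant adverse reactions, complications or illness needing urgent care, and unspecified further reasons. None of these has a pain threshold, and none is tied to an arm.

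The Intervention section assigns each subject to EA or to drug treatment. Under Medication group, "participants undergo treatment through the oral ingestion of pregabalin capsules" only, and the Conclusion describes the comparator in the same way ("a clear and stable advantage over oral pregabalin alone"). No sham or background acupuncture is described for that arm.

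The Blinding section exempts the needling operator and then states that "blinding is implemented for all other personnel involved in the study". The randomization section describes the evaluation of efficacy "with a triple separation of the researcher, the acupuncture operator, and the statistician".

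The Elimination criteria remove, among others, "Self-withdrawal or loss of visits by subjects". For those removed, "their study medical records should be retained for review and not included in the final statistical analyses". Discontinuation for pain is not named as a ground for removal.

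**The concern.** A stopping rule based on the outcome variable should work the same way in both arms. As worded, an EA patient above VAS 8 meets a stated exit, and a pregabalin patient with the same pain does not. That patient can leave only through general or patient-initiated routes. This is a gap in patient protection as well as a source of unequal handling.

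The second problem is internal consistency. Nobody can judge whether pain persisted despite acupuncture without knowing that acupuncture was given, yet the physician who makes that judgement falls within the group that the Blinding section says is unaware of the grouping.

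What is at stake for the analysis is conditional. VAS is the primary outcome, and the Sample size estimation section uses the proportion with VAS ≤ 2 after 4 weeks. If patients stopped for severe pain have no week-4 VAS, or are dropped as lost visits, treatment failures leave the denominator. If this happens more in one arm than in the other, the comparison is distorted.

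**Working it through.** **Step 1: can the rule apply to both arms?**
- Condition: pain persisting after acupuncture, with VAS above 8 (Discontinuation criteria, first item).
- EA arm: receives acupuncture, so the condition can be met.
- Drug arm: pregabalin only (Medication group; Conclusion), so the condition cannot be met as written.
- No other item has a VAS threshold, so no parallel rule exists for the drug arm.

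**Step 2: can the rule be applied blind?**
- Decision-maker: the physician responsible for diagnosis.
- Information needed: whether the patient had acupuncture, which is the allocation.
- Blinding section: only the needling operator knows the allocation.
- Read literally, the two statements cannot both hold.

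**Step 3: do such exits leave the analysis?**
The document does not settle this. Pain discontinuation is not an elimination ground, but a patient who stops and does not return could be classed as a lost visit, or could have no week-4 VAS. The calculations below therefore illustrate one possible handling and do not estimate what will happen.

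**Step 4: illustration for VAS ≤ 2.**
Inputs from Sample size estimation: 62 per arm, and a success rate of 74.4% (the pregabalin rate), here set equal in both arms so that there is no true effect. Assumption: a mean of k pain exits per arm, all of them failures and all omitted.

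Model per arm: exits e ~ Binomial(62, k/62); successes among the 62 − e who remain ~ Binomial(62 − e, 0.744/(1 − k/62)). EA is declared better if the pooled two-proportion z exceeds 1.96. The probabilities come from exact enumeration.

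The apparent EA success rate is 0.744 × 62/(62 − k):
- k = 1: 46.128/61 = 75.6%
- k = 2: 46.128/60 = 76.9%
- k = 3: 46.128/59 = 78.2%

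| Mean exits, EA | Mean exits, drug | One-sided false-positive rate |
|---|---|---|
| 0 | 0 | 2.5% |
| 1 | 0 | 3.6% |
| 2 | 0 | 5.0% |
| 3 | 0 | 7.0% |
| 3 | 1 | 5.2% |
| 3 | 2 | 3.7% |
| 3 | 3 | 2.5% |
| 1 | 3 | 1.1% |

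If pain exits are kept as not reaching VAS ≤ 2, the denominators stay at 62 and the rate is 2.5%, as in the first row.

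**Step 5: illustration for the VAS score.**
Omitting k patients with VAS v from an arm of 62 with mean m lowers that arm's mean by k(v − m)/(62 − k). Neither m nor v is in the document. With m = 3 and v = 9 assumed:
- k = 1: 6/61 = 0.10
- k = 2: 12/60 = 0.20
- k = 3: 18/59 = 0.31

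Over m from 2 to 4 and v from 8.1 to 10, the ranges are 0.07 to 0.13, 0.14 to 0.27 and 0.21 to 0.41 points.

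**The case against.** The strongest reply is that this is a drafting slip. The first item opens neutrally, with exacerbations in any patient, and the Blinding section also speaks loosely of acupuncture when it means patients in general. Drug-arm patients in severe pain can still leave through the urgent-care item, the general last item or self-withdrawal. Much of this stands: the document shows no deliberate one-arm policy. It does not remove the point, because investigators apply the rule as written, and a fixed threshold in one arm with discretion in the other is not equal handling.

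A reader might infer that the deciding physician is unblinded. No section says so. What the text supports is a conflict between the stopping rule and the Blinding section.

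A reader might also infer that the trial is biased toward EA. The document does not support that. It gives no exit rates, does not say that pain exits are removed, and leaves arm-neutral routes through which drug-arm failures can go. The false-positive figures fall on both sides of 2.5%, and they reflect omission from the analysis more than the wording itself.

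The EA safety list ("Broken needles, missed needles, needle fainting, unbearable acupuncture-induced pain") might look like further evidence of one-sided pain handling. It is not: it records pain caused by needling, which cannot arise in the drug arm, and it is not a stopping rule.

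**Conclusion.** The point holds on the wording. The only pain-severity stopping rule cannot, read literally, apply to the pregabalin arm, and applying it requires knowledge of the arm that the Blinding section denies to everyone but the needling operator. This rests on the text alone and needs no numerical assumption.

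The effect on the results is not established. It arises only if exits differ by arm and are left out of the analysis. Under the assumed counts of up to three exits per arm, the false-positive rate runs from 1.1% to 7.0%, so neither size nor direction is fixed. The correction is worth making because the rule is operative and the change is nearly free, not because a particular bias has been shown.

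Rewording this rule does not repair the blinding as a whole. One arm has needling sessions and the other takes capsules, and the Limitations section concedes that patients may work out their treatment. It removes only the conflict created by this clause.

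**What to change.** 1. In the first discontinuation item, replace the reference to acupuncture with study treatment, and apply the same VAS above 8 criterion in both arms.
2. Apply it at the scheduled VAS assessments during treatment (Table 1: weeks 2 and 4). EA patients attend three times a week and drug patients take capsules at home, so a trigger that also used reports between visits would pick up more exits in the EA arm.
3. Keep the physician's severity evaluation, made without reference to the arm. The eligibility criteria set a pain floor of 4 and no ceiling, so a threshold with no clinical judgement could stop a patient who entered above 8 and has not yet improved.
4. Treat the exit as stopping study treatment, and still record VAS at the remaining scheduled visits.
5. In the VAS ≤ 2 analysis, count patients in either arm who exit for pain before week 4 as not reaching VAS ≤ 2, and state that the elimination rule does not remove them.

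The cost is one amended sentence and one analysis rule, with no additional patients or visits. Reported success rates may be slightly lower, and patients who stop treatment must still be followed at visits already scheduled.

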### Sample size estimation

This research involves a randomized controlled trial design, where eligible participants will be allocated to two distinct groups in an equal proportion of one participant to another (1:1 ratio), and the primary outcome metric is the percentage of cases with a pain intensity VAS ≤ 2 points after 4 weeks of treatment. According to the project team’s pre-efficacy observation pre-trial, the effective rate of this study’s treatment regimen in treating PHN is about 91%, and the literature reported that the effective rate of pregabalin is 74.4% (49). The estimation of the required sample size formula for the test of superiority of the independent sample rate of two groups is used for the calculation, taking *α* = 0.025 and *β* = 0.2, with the same number of sample cases between the groups, and using a one-sided test, taking into account a 20% dropout rate. Each group will necessitate a minimum of 62 cases, resulting in a combined total of 124 cases across the two groups.

$$N=\frac{2{\left[Z_{\alpha /2}\sqrt{2\bar{p}\bar{q}}+Z_{\beta }\sqrt{p_{0}q_{0}+p_{1}q_{1}}\right]}^{2}}{{\left(p0-p1\right)}^{2}}$$

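### The only pain-score stopping rule is worded for the electroacupuncture arm alone and acts on the primary outcome scale

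*Protocol article*

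**What the plan says.** The Discontinuation criteria list four grounds, and only the first concerns pain. It opens without naming an arm: "A physician responsible for diagnosis assesses exacerbations of PHN occurring during the study". It then ties its one numeric threshold to "facial pain symptoms that persisted despite acupuncture treatment, as indicated by a VAS score exceeding 8", after which "the physician evaluates the severity and subsequently discontinues the study". The other three grounds (significant adverse reactions, severe complications or illness, and other reasons that prevent continuation) carry no pain score.

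The Intervention section gives each participant one of the two treatments. Under Medication group, "participants undergo treatment through the oral ingestion of pregabalin capsules", with no other treatment.

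The Elimination criteria form a separate list. They include "Self-withdrawal or loss of visits by subjects", fewer than two treatments, and serious adverse reactions or events during treatment. A note says that eliminated subjects are "not included in the final statistical analyses". Discontinuation for high VAS is not on this list.

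The VAS is the primary outcome. The Sample size estimation section uses it as a responder endpoint: "the percentage of cases with a pain intensity VAS ≤ 2 points after 4 weeks of treatment".

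**The concern.** A stopping rule that reads the primary outcome scale should apply identically in both arms. This one is conditioned on acupuncture having been given, so a pregabalin patient above VAS 8 does not satisfy it. That patient can still leave through the arm-neutral grounds or by withdrawing, but no fixed score prompts it.

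Two things are at stake:

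- **Bias.** A patient above VAS 8 during treatment is very unlikely to reach VAS ≤ 2 at week 4. If such patients lose their week 4 assessment or are dropped from the analysis, the EA arm sheds failures under a written rule while the drug arm sheds them only by discretion. The EA response rate then rises with no treatment effect behind it, in a trial designed to show EA superior.
- **Patient protection.** Drug-arm patients in severe pain lack the explicit safeguard that EA patients have.

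**Working it through.** **Is the rule really one-sided?** I looked for any other pain threshold that could serve the drug arm.

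- Discontinuation criteria: one VAS threshold, conditioned on acupuncture.
- Safety evaluation related to EA: a VAS of 8 or more appears, but it grades pain caused by needling. It is a safety item, not a stopping rule.
- Pregabalin adverse reactions: a list of symptoms with no pain score.
- Inclusion criteria: a baseline facial pain score of at least 4 with no upper limit, so patients can enter close to the trigger.

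No threshold for the pregabalin arm exists in the document.

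**How could it reach the analysis?** The route has three steps: the trigger is applied in the EA arm only; the stopped patient has no later visits; and the patient is then treated as lost to visits and eliminated. The first step follows from the wording. The second is likely, because the criterion speaks of discontinuing the study rather than the treatment. The third is a plausible reading that the protocol does not state.

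**Size if all three steps occur.** The protocol gives no figure to reproduce, so this is an illustration.

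Inputs:

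- n = 62 per arm (Sample size estimation).
- True response p = 0.744 in both arms (the protocol's pregabalin rate), so there is no true difference.
- r = fraction of EA patients stopped and excluded, all of them failures. This is assumed; the documents do not say how many would exceed VAS 8.
- Pooled two-proportion z-test, upper critical value 1.96 (one-sided 2.5%).

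Formulas:

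- Apparent EA rate = p/(1 − r). For r = 5%: 0.744/0.95 = 0.783, a rise of 3.9 points.
- Share of EA failures removed = r/(1 − p). For r = 5%: 0.05/0.256 = 19.5%.
- EA patients removed = 62r. For r = 5%: 3.1.

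The error rates come from simulation with at least 1,000,000 trials per setting.

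| r | EA patients removed | Share of EA failures removed | Apparent EA rate | Rise (points) | One-sided error, no drug-arm removal | One-sided error, drug arm at half the EA rate |
|---|---|---|---|---|---|---|
| 0% | 0 | 0% | 74.4% | 0 | 2.5% | 2.5% |
| 1% | 0.6 | 3.9% | 75.2% | 0.8 | 3.1% | 2.8% |
| 2% | 1.2 | 7.8% | 75.9% | 1.5 | 3.9% | 3.2% |
| 5% | 3.1 | 19.5% | 78.3% | 3.9 | 7.2% | 4.5% |
| 10% | 6.2 | 39.1% | 82.7% | 8.3 | 19.0% | 8.4% |

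Two controls isolate the cause. With equal removal in both arms the error is 2.5–2.6% throughout. With nobody removed and all stopped patients counted as non-responders it is 2.4–2.5%. The inflation therefore comes from unequal exclusion, not from the stopping rule as such.

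**The case against.** The strongest reply is that this is a drafting slip. The criterion begins with exacerbations in general and speaks of a patient, not an EA patient. The Blinding section says that everyone except the needling operator is unaware of allocation, so a blinded physician could not apply an EA-only rule. Applied to all patients, the rule is symmetric and the error stays at about 2.5%. A slip is quite possible. But sites follow the text, and a rule that requires knowledge of the arm conflicts with the blinding plan, which is a further reason to reword it.

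Second, elimination of these patients is not stated, and the trigger is not automatic because the physician first judges severity. Both points stand and make the inflation conditional. They do not remove the asymmetry, and discontinuing the study can by itself leave an EA failure without a week 4 VAS.

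Third, r has no source in the documents. Zero drug-arm removal is a limiting case, since those patients can also leave, and r = 10% is extreme. At r = 1–2% with half-rate removal in the drug arm, the error is only 2.8–3.2%. The 62 per arm also already includes a 20% dropout allowance, and the calculation covers the responder endpoint, not an analysis of the VAS score itself. All of this is fair: the table shows direction and scale, and does not forecast.

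Fourth, the net direction over all exclusions is unknown. Elimination for serious adverse events could remove drug-arm patients too, and the exclusion note is the deeper defect. That also stands. Correcting the exclusion note would remove most of the bias, but it would not give pregabalin patients a matching threshold.

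**Conclusion.** The point holds. The only numeric pain trigger for discontinuation is worded so that it can apply only to EA patients, it acts on the primary outcome scale, and no equivalent exists for pregabalin. That much rests on the text alone.

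The effect on the result is conditional. It requires that stopped EA patients lose their week 4 assessment or are eliminated, and that drug-arm failures are removed less often. Under those assumptions, removing one to three EA patients moves the one-sided error from 2.5% to about 3.9–7.2% with no drug-arm removal, or about 3.2–4.5% with half-rate removal. If removal is equal, or these patients are kept as non-responders, there is no inflation. The change should be made; confidence that the bias would occur in practice is moderate.

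**What to change.** 1. In the Discontinuation criteria, make the trigger arm-neutral: pain persisting *despite study treatment* with VAS above 8, in either arm, judged without reference to allocation.
2. Separate stopping treatment from leaving the study. After treatment stops, continue to collect VAS at the remaining scheduled visits, including weeks 4, 8 and 12.
3. Keep these patients in their randomised arm. Count them as not reaching VAS ≤ 2 at week 4 for the responder endpoint, and use their collected scores in any analysis of the VAS itself.
4. Add a sentence to the Elimination criteria that discontinuation under the preceding section is not elimination.

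The cost is a few words in two sections and visits that are already scheduled. The EA estimate may become slightly less favourable.

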### Quality control and data management

First of all, the research group will formulate the unified Standard Operating Procedures (SOPs), and prior to the official commencement of the clinical trial by 1 month, the research team will organize a dedicated training session aimed at imparting standardized training to all researchers participating in the study. The core emphasis of the training revolves around the project’s execution plan and the adherence to various SOPs. This is to ensure that every clinical researcher is thoroughly acquainted with the research methodology, including the intricate implementation details, thereby guaranteeing the credibility and authenticity of the clinical research findings.

Furthermore, all observations recorded during clinical studies must undergo rigorous verification and multiple rounds of confirmation to uphold the reliability and authenticity of the data. This approach ensures that every result and conclusion presented in clinical studies is derived solely from the primary, unadulterated data, maintaining the integrity of the research outcomes. Expert data administration companies are commissioned to conduct clinical data management, and monthly clinical research quality checks are strictly implemented. Reasons for withdrawal will be systematically recorded for all participants who discontinue the trial at any stage, and the resulting dropout rate will be statistically analyzed.

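### The discontinuation criteria stop the study rather than only the treatment, so week-4 VAS can be lost for outcome-related reasons, and the pain criterion as worded covers only the EA arm

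*Protocol article*

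**What the plan says.** Discontinuation criteria in the protocol article lists four grounds.

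- **Pain.** It applies "when a patient experiences facial pain symptoms that persisted despite acupuncture treatment", shown by a VAS above 8, and "the physician evaluates the severity and subsequently discontinues the study".
- **Significant adverse reactions.** A specialist assesses them "to make a decision on whether to proceed or discontinue the research".
- **Complications.** "Participants who encounter severe complications or illnesses during the study that necessitate urgent medical attention". No action is written beyond the heading.
- **Other reasons.** Patients who for some further reason cannot carry on in the study.

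Quality control and data management describes the people concerned as leaving the trial: "Reasons for withdrawal will be systematically recorded for all participants who discontinue the trial at any stage". It adds that the dropout rate will be analysed.

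Elimination criteria names "Self-withdrawal or loss of visits by subjects", fewer than two treatments, and serious reactions or events while on treatment. For all of these, "their study medical records should be retained for review and not included in the final statistical analyses".

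Table 1 schedules the VAS at baseline and at weeks 2, 4, 8 and 12. Sample size estimation takes the proportion with VAS of 2 or less after 4 weeks as the primary metric.

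**The concern.** Stopping the allocated treatment and leaving the study are different events. A patient can stop needling or capsules and still mark a VAS at week 4. The article does not make this distinction: where it states a consequence, the consequence is at the level of the study.

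This matters because the reasons for stopping are tied to the outcome. The pain criterion is triggered by the primary outcome scale itself. A patient above 8 is, at that moment, far from the success mark of 2 or less, yet would leave instead of being measured at week 4. Stops for adverse reactions also depend on the treatment, and needling and pregabalin have different adverse reactions.

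The pain criterion also refers only to acupuncture. Read literally, it takes poor responders out of the EA arm and leaves their counterparts on pregabalin in place.

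Who is measured and who is analysed are separate questions. Repairing the analysis set alone would leave an all-randomised analysis without readings for these patients.

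**Working it through.** **1. The passages side by side**

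| Ground | Written consequence | Treatment-only stop offered? |
|---|---|---|
| VAS above 8 despite acupuncture | Physician evaluates, then the study is discontinued | No |
| Significant adverse reaction | Discretionary: go on, or stop the research | No |
| Severe complication or illness | None stated, but under the same heading | No |
| Other reasons | Cannot carry on in the study | No |

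Elimination criteria does not name a physician-directed stop for pain. Such a patient is removed if treated as withdrawn, as having missed visits, or as having had fewer than two treatments. A patient stopped for a serious reaction is removed outright, even if a VAS had been taken.

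**2. Which readings are at risk**

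Treatment lasts 4 weeks. A stop before week 4 loses weeks 4, 8 and 12, and week 2 as well if it comes early enough. A stop after the week-4 reading loses week 8, week 12 or both, but not the primary time point.

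**3. Possible size**

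The plan gives no expected rate of stops for pain or harm. Its only figure is a general 20% dropout allowance. The loss rates below are therefore assumptions.

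Inputs from Sample size estimation: success 74.4% on pregabalin, 91% on EA, 62 patients per arm. The 62 is taken as stated, since this point does not depend on how it was derived.

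Let p be the true success rate and l the fraction of the arm lost. If all lost patients are non-successes and leave the denominator:

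observed rate = p / (1 − l)

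*No true difference, 74.4% in both arms, loss in EA only:*

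- l = 5% (0.05 × 62 = 3.1 patients): 0.744 / 0.95 = 78.3%, a spurious difference of 3.9 points.
- l = 10% (0.10 × 62 = 6.2 patients): 0.744 / 0.90 = 82.7%, a spurious difference of 8.3 points.

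The false-positive risk follows from the normal approximation Φ[(d − 1.96 × se0) / se1]. Here d is the spurious difference, se0 the pooled standard error and se1 the unpooled one, with 62(1 − l) EA patients against 62. At a nominal one-sided 2.5% it is about 7% for l = 5% and about 19% for l = 10%.

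*Planned rates, 91% against 74.4%, true difference 16.6 points:*

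- 5% loss in EA only: 0.91 / 0.95 = 95.8%, so the difference reads 21.4 points.
- 10% loss in the drug arm only: 0.744 / 0.90 = 82.7%, so the difference reads 91 − 82.7 = 8.3 points.

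The direction thus depends on which arm loses patients.

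**4. Where the shift vanishes**

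- If lost patients succeed at the same rate as the rest, the observed rate stays at p.
- If non-successes who stop are kept in the denominator as non-successes, the rate also stays at p.

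**The case against.** The strongest reply is that much of this is inferred. Only the pain criterion directs a stop. The adverse-reaction criterion allows the patient to go on, and the complications criterion states no action, so it would be wrong to say that every criterion ends participation. Nor does Quality control and data management say that outcome collection ends; it says that reasons are recorded. The article condenses a fuller protocol, which may provide for later assessments. All of this stands. What remains is that the criteria are worded at study level, and no section of the article provides for a VAS after discontinuation.

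A second reply is that Elimination criteria is the controlling problem: the shifts above arise only when stoppers leave the denominator. That is right, and it is why the fix must cover both sections.

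A reader might infer four stronger things that the documents do not support.

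- **Adverse events behind a stop are not followed to their end.** No section says this, and Safety evaluation has safety indicators recorded throughout treatment and follow-up.
- **No analysis could recover the loss.** For a VAS of 2 or less, counting stoppers as non-successes is an ordinary analysis.
- **The bias is about 18 points**, from 46/62 (74%) becoming 46/50 (92%). This assigns the whole 20% dropout allowance to these criteria and makes every lost patient a non-success. At the planned EA rate only 0.09 × 62 = 5.6 patients are non-successes, so 12 could not be lost from that arm.
- **Continued follow-up would gain about 7 points of power** (62.4% with 50 per arm to 69.6% with 62). This assumes that recovered patients succeed at the planned rates, so that the loss is uninformative, which contradicts the bias argument.

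**Conclusion.** The point holds in a limited form. The discontinuation criteria are framed at study level and offer no stop of treatment with continued assessment. Together with Elimination criteria, a stop before week 4 would lose the primary reading for reasons linked to pain or harm. The pain criterion as worded applies only to EA, and losing poor responders from that arm alone could favour EA.

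The size cannot be fixed from the documents, because the rate of such stops is not given. With assumed EA-only losses of 5% and 10%, all non-successes and all outside the denominator, a true 74.4% would show as 78.3% and 82.7%. If those lost are average patients, there is no shift. These figures show how sensitive the comparison is; they do not forecast the bias.

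The change should be made as a cheap improvement. It has to be made prospectively, because readings not taken cannot be collected later.

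**What to change.** 1. In Discontinuation criteria, define stopping the allocated treatment separately from leaving the study. No clinical stopping threshold needs to change.
2. Reconcile the pain criterion with the two-arm design: state which arms it covers and, if only EA, why.
3. State that patients who stop treatment keep the VAS and adverse-event assessment at the existing Table 1 visits (weeks 2, 4, 8 and 12), unless they withdraw consent to assessment.
4. Amend Elimination criteria so that these readings enter the primary comparison. Without this step, the readings would be collected and then discarded.

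The cost is protocol and consent wording. The visits already exist, and no extra patients are needed. The downside is that some readings will be taken off the allocated treatment, so the estimate describes the effect of a treatment policy and not of treatment taken in full. The protocol should say so.
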